**Intervention**

**BA tele-trial intervention group**

We will recruit approximately 30 people in custody in the intervention group who will receive BA plus usual prison health care (20). The intervention will be delivered by the custodial health nurses who will receive ongoing clinical supervision from an expert in BA via a telehealth video link. The people in custody will be offered twelve sessions of BA, which will be delivered twice weekly, in 30-minute sessions, for six weeks. Specific BA techniques that will be applied include (a) identification of depressed behaviours (b) analysis of the triggers and consequences of depressed behaviours (c) monitoring of activities (d) development of alternative goal-orientated behaviours (e) scheduling of activities, and (f) the development of alternative behavioural responses to rumination.

**TAU group**

People in custody allocated to the control group will receive the usual prison health care alone. No other specific intervention will be provided to this group. Across sites, TAU will be composed of 30 participants (20).

The CONSORT diagram illustrating participant flow is shown below (Figure I).

[figure not shown]

**BA training**

The training in BA techniques is an academically accredited online “Professional Certificate in BA for Depression” program offered by the University of South Australia. The 10-week online training program consists of five modules: (a) the evidence base of BA (b) introduction to BA (c) assessment and mood monitoring (d) functional analysis, and (e) activity scheduling. BA experts, MJ, SD, and SW facilitate the training.

Custodial health nurses who have completed the Professional Certificate are expected to have achieved the following learning outcomes: (a) gained a sound understanding of the BA intervention (b) attained the relevant core BA skills, and (c) demonstrated competency in BA delivery.

Custodial health nurses who join the trial have completed the training and will deliver BA to participating people in custody, with supervision being provided via telehealth by MJ, SD, and SW. Each custodial health nurse will deliver BA to at least five people in custody for the duration of the trial.

**Intervention fidelity**

We will assess the quality of and adherence to the BA treatment protocol via the telehealth supervision and support structure.

**Evaluation**

**Feasibility**

The study feasibility outcomes will be evaluated as follows:

- Determine the proportion of eligible people in custody with depressive symptoms who are approached and agree to participate in the trial.
- Determine the proportion of eligible people in custody who have agreed to participate and agree to be randomised.
- Determine the proportion of people in custody with depressive symptoms that complete baseline measures.
- Determine the proportion of people in custody who complete a co-delivered Tele-trial Behavioural Activation treatment (attending for a minimum of six sessions over six weeks).
- Determine the proportion of people in custody who complete outcome measures at six weeks and three-month follow-up.
- Establish SAPHS nurses’ fidelity to Behavioural Activation treatment.
- Calculate the preliminary efficacy of Behavioural Activation on the primary clinical outcome measure.
- Explore SAPHS nurses’ experiences of delivering a co-delivered tele-trial Behavioural Activation treatment to the people in custody.
- Explore SAPHS nurses’ experiences receiving co-delivered tele-trial Behavioural Activation training and supervision.
- Determine the proportion of people in custody with depressive symptoms that participate in the tele-trial improve their health-related quality of life outcomes (clinical outcome measure).
- The number of adverse events and harms that occur during the trial.

**Process evaluation (acceptability and satisfaction)**

Individual, semi-structured interviews will be conducted with a purposively sampled subset of custodial health nurses (minimum of 6) and people in custody with depressive symptoms (minimum of 10) to explore their experiences of involvement in the trial. Interviews will be conducted with custodial health nurses to gain insight into their experiences of completing the BA training program and delivering the BA treatment. The custodial health nurses will also be invited to share their experience of the supervision provided by the BA experts via a telehealth platform.

The interviews with people in custody with depressive symptoms will focus on their experiences of, and perceived impact of, engaging in the BA treatment. General topic areas (for people in custody and custodial health nurses) will include what worked; what did not work; what could be done differently; what could be improved; and what were the facilitators and barriers to engaging with BA.

The interviews will be conducted by the research tele trail nurse, (in-person or by phone), audio-recorded (where feasible), and are anticipated to last no more than 30 minutes. Data collection will cease once the information becomes too repetitive and no new insights are added by the interviews. An interview topic guide will be developed for each group of interviewees.

**Preliminary intervention effects (primary and secondary outcomes)**

**Clinical outcome measure- depression**

The first clinical outcome will be a change in depressive symptoms as assessed by the tele-trial research nurse using the PHQ-9 scale.

*Primary Health Questionnaire Nine (PHQ 9)*. Depressive symptoms will be measured with the Primary Health Questionnaire Nine (PHQ 9) (21, 22). The PHQ 9 is a 4-point Likert-type scale (0, absent; 1, mild; 2, moderate; 3, severe) with nine items that correspond to the DSM-IV Diagnostic Criterion A symptoms for major depressive disorder (23). A meta-analysis rated the PHQ-9 scale as being reliable with a sensitivity of 88% and a specificity of 78% at a cut-off of 10 or above (24).

The clinical outcome measure will be implemented at three-time points (a) at baseline (0 weeks), (b) at 6 weeks post-intervention, and (c) at 3 months post-intervention.

**Clinical outcome measure- quality of life**

The second clinical outcome will be the level of health-related quality of life as measured by the 36-Item Short Form Health Survey (SF 36) (25) The SF 36 measures physical functioning, role physical, bodily pain, general health, vitality, social functioning, role emotion, and mental health (25). In this study, we will administer the SF 36 questionnaire at three-time points: (a) at baseline (0 weeks), immediately after postintervention (6 weeks), and (c) at three months post-intervention.

Completion of eight (8) out of 10 sessions will be deemed to constitute treatment engagement and completion. Acceptability of the treatment will be determined from perceptions of satisfaction with and benefits from the BA treatment obtained through interviews with people in custody.

Other data to be collected

*Sociodemographic Questionnaire*

Demographic information about gender, date of birth, marital status, educational level and type of prison pathway the person in custody is located will be collected by the tele-trial research nurse at the assessment and recruitment stage (Attachment XVII).

*Contextual factors*

We will collect information about each participating tele-trial site at baseline and 6 weeks post-intervention. The information will be important in understanding the implementation process. These factors (including organisational changes, staffing changes, etc), will be collected by the tele-trial research nurse through conversations with the custodial health nurses and the nurse unit managers at the four participating prisons.

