**Method**

A sample of 60 people in custody aged over 18 years or older with presenting symptoms of depression as assessed using the PHQ 9 scale (with a score of 5-14 mild to moderate depression) will participate in the trial. Recruited people in custody will be randomised to receive BA plus treatment as usual (TAU) or TAU for depression provided by custodial health nurses. Eight custodial health nurses will be recruited from four rural prisons in South Australia. The custodial health nurses will be prepared to deliver Behavioural Activation to people in custody at the selected prisons. The BA intervention will involve preparing people in custody to monitor their mood, identify triggers that can impact mood, identify activities that may enhance mood, and enable each participating person in custody to formulate an activity schedule. BA will involve twelve conversations with people in custody held twice weekly over six weeks. Changes in depressive symptoms and health-related quality of life will be assessed at three-time points: (a) at baseline, (b) 6 weeks, and (c) 3 months post-intervention. We will use descriptive statistics to report changes over time, but not make any judgement. In addition, we will interview custodial health nurses and people in custody to understand further BA acceptability and feasibility in prison settings.

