**Statistical analyses**

All data will be entered and analysed descriptively. The primary analysis is intended to determine whether conducting a subsequent fully powered RCT is feasible. Therefore, the analyses will be descriptive by exploring all feasibility outcomes and will include measures of uncertainty, such as 95% CIs. As feasibility trials are not designed to establish efficacy, we will estimate the variance of outcome measures and calculate the effect size differences (with 95% CIs) on outcome measures from baseline to both follow-up points (on an intention-to-treat basis) in both groups. Where appropriate, the generalised estimating equation (GEE) will be employed to analyse the preliminary effects of BA across the two time points (baseline and 6 weeks). The GEE analysis will account for intra-correlated repeated outcome data and accommodate data missing at random.

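### Completion of BA treatment, a listed feasibility outcome, has two incompatible definitions (at least six sessions; eight out of 10), and the 10 does not match the twelve sessions offered

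*Protocol*

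**What the plan says.** Completion is defined in three places in the protocol, and the length of the course in two.

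- Objectives, People in custody, item 5, and the Feasibility list under Evaluation both take the proportion who complete treatment, defined as "attending for a minimum of six sessions over six weeks".
- The section on the quality-of-life outcome measure states: "Completion of eight (8) out of 10 sessions will be deemed to constitute treatment engagement and completion".
- The intervention section states: "The people in custody will be offered twelve sessions of BA, which will be delivered twice weekly, in 30-minute sessions, for six weeks". The abstract's Method paragraph agrees: "BA will involve twelve conversations with people in custody held twice weekly over six weeks".

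The Statistical analyses section says: "The primary analysis is intended to determine whether conducting a subsequent fully powered RCT is feasible". It provides for the feasibility outcomes to be described with 95% confidence intervals. The BA arm, in which completion is measured, is planned at about 30 people.

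**The concern.** Both rules define completion of the same treatment, and they disagree on the threshold (six or eight) and on the session total (twelve or 10). The document does not rank them or say that they measure different things. The proportion completing BA therefore has no unique value, even with perfect attendance records. A confidence interval does not help, because it describes sampling error around a proportion whose numerator has not been fixed. As the text stands, the choice could be made after attendance is known.

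This is not a detail that the protocol leaves to a statistical analysis plan. The protocol fixes both definitions itself, so an analysis plan that adopted either one would contradict part of the protocol.

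**Working it through.** **Session total.** 2 sessions per week × 6 weeks = 12. This reproduces the twelve sessions in the abstract and the intervention section. It does not reproduce the 10 in the quality-of-life section.

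**Thresholds as a share of the course.**

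- At least six of the twelve offered: 6/12 = 50%.
- Eight out of 10 as printed: 8/10 = 80%.
- Eight applied to the twelve offered: 8/12 = 67%.
- If the 80% were carried over instead, 0.8 × 12 = 9.6, which means ten sessions.

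The sentence with the 10 therefore cannot be applied without interpretation. The comparison below uses six against eight of the twelve offered, since that is the course participants receive.

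**Who is classified differently.** The two rules disagree on exactly those who attend six or seven sessions. The gap between the two completion rates is the share of the BA arm in that group.

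**Size of the gap.** The protocol gives no attendance rate. I assume a mean per-session attendance p from 0.5 to 0.9 and show two models for X, the number of sessions attended out of 12:

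- Independent sessions: X ~ Binomial(12, p).
- Attendance varying between people: X ~ Beta-binomial with mean p and intraclass correlation 0.3, so a = p(1 − 0.3)/0.3 and b = (1 − p)(1 − 0.3)/0.3. At p = 0.6, a = 1.40 and b = 0.93.

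In each case the gap is P(X ≥ 6) − P(X ≥ 8).

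| Assumed attendance | Independent: ≥6 | ≥8 | Gap (points) | ICC 0.3: ≥6 | ≥8 | Gap (points) |
| --- | --- | --- | --- | --- | --- | --- |
| 50% | 61.3% | 19.4% | 42 | 54.2% | 37.5% | 17 |
| 60% | 84.2% | 43.8% | 40 | 67.3% | 51.1% | 16 |
| 70% | 96.1% | 72.4% | 24 | 79.0% | 65.3% | 14 |
| 80% | 99.6% | 92.7% | 7 | 88.5% | 79.0% | 10 |
| 90% | 100.0% | 99.6% | under 1 | 95.6% | 90.9% | 5 |

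In people, with 30 in the arm and independent sessions, expected completers are 30 × 0.842 = 25.3 against 30 × 0.438 = 13.1 at 60% attendance, and 29.9 against 27.8 at 80%.

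**Comparison with sampling error.** The 95% half-width at n = 30 and a proportion of 50% is 1.96 × √(0.25/30) = 0.179, about 18 points. With independent sessions the gap exceeds this at 50% to 70% attendance and falls below it at 80% and above. With an intraclass correlation of 0.3 it is slightly below it at 50% and 60%, and smaller after that.

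**The case against.** Three arguments limit the point.

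**The two rules might measure different things.** The later sentence speaks of engagement as well as completion. But it also uses the word completion, for the same treatment, and nothing in the protocol separates the two constructs. This argument does not stand.

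**The effect could be made to look much larger than it is.** A reader might take the 10 literally and compare at least six of twelve with at least eight of 10. At 60% independent attendance that gives 84% against 17%, about 68 points. The documents do not support this as a measure of size: it compares courses of different length, and the trial offers no 10-session course. On the twelve sessions offered, the gap is small when attendance is high, and with strong variation between people it never exceeds the 18-point half-width. This argument stands and limits the size of the point.

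**Nothing in the protocol turns on the number.** A reader might infer that the same data could be declared feasible under one rule and not feasible under the other. The protocol states no target completion proportion, plans a descriptive analysis, and lists completion as one of eleven feasibility bullets without calling it a main outcome. So no stated verdict flips, and this argument also stands.

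None of these arguments removes the contradiction. It is in the current running text, and it leaves a listed outcome without a unique definition.

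**Conclusion.** The protocol is wrong as written on this point: one listed feasibility outcome has two incompatible definitions, and one of them uses a session total that does not fit the trial's schedule. This rests on the text alone and needs no assumption.

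The size does rest on assumptions. Over 50% to 90% assumed attendance, the reported completion rate shifts by about 42 points down to under 1 with independent sessions, and by about 17 down to 5 with an intraclass correlation of 0.3. Neither attendance nor its variation between people is given in the protocol. The Limitations section does expect lockdowns, staff shortages and limited therapy space to restrict attendance, so the high-attendance end, where the gap nearly vanishes under independence, cannot be taken for granted.

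The correction is needed because the outcome is not uniquely defined. Which threshold or session count is right is not judged here.

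**What to change.** Reconcile item 5 of the objectives for people in custody, the Feasibility list and the completion sentence in the quality-of-life section with the session count in the abstract and the intervention section. State one completion threshold, once, over the number of sessions actually offered, and have the other places refer to it. The investigators should choose the threshold and record it before any attendance data are examined.

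Report that proportion with its 95% confidence interval, together with the distribution of sessions attended from none to the full number offered. The distribution lets a reader see the result under any other cut-off.

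The cost is a short correction to the text and one extra table. It needs no new data beyond the count of sessions attended, which either definition already requires.

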**Data collection and management**

The data manager will facilitate the data collection process. With prior written consent, participant demographic information will be collected through the tele-trial sites. For the primary outcome (depressive symptoms), the data will be collected at (a) baseline, (b) 6 weeks, and (c) 3 months post-intervention. The secondary outcome data (health-related quality of life outcomes) will be collected at a) baseline, (b) 6 weeks, and (c) 3 months post-intervention. With permission from people in custody, outcome data will also be collected and analysed from those that discontinue the study or deviate from the intervention protocol.

The interviews with the people in custody and the custodial health nurses will be audio-recorded (where feasible) with permission from the interviewees. The audio recordings will be transcribed verbatim by independent transcribers that are contracted to the University of South Australia. The transcription service signed confidentiality and data security agreements with the university. Transcriptions will be de-identified by the research team before data analysis to ensure anonymity.

The study will collect individually identifiable data (e.g., Consent forms, audio-recordings), non-identifiable data (survey data), and re-identifiable data from which identifiers would have been removed. These types of data will be securely stored with the individually identifiable data kept separately from other research data to maintain confidentiality and anonymity. For example, the audio recordings and corresponding transcripts will be assigned codes that will be kept separately.

Should the need arise to re-identify data, CI KT or PI MJ will be responsible.

All electronic data will be stored securely on the university’s server and files will be password protected. Only the relevant members of the research team will have access to these files. All paper copy data will be kept in lockable drawers at the Whyalla campus of the University of South Australia. Data will be managed following the National Statement on Ethical Conduct in Human Research (26) and the University of South Australia Research Data Management Procedures. De-identified data person in “custody data” and deidentified location data will be made available upon written request, to enable trial checking and reuse.

All the data we collect will be de-identified. Participants' identities will remain confidential. The subject identification log will be kept separately. Chief Investigator (CI) KT and PI MJ will be responsible for de-identifying the data. This will be done by reviewing and removing direct identifiers. Each participant will then be allocated a study number/code. The participant identification code will be kept separately. CIs involved in data analysis and reporting will only have access to the de-identified data; only CI KT and PI MJ will have access to the identification code. Data will be stored on a secure data storage and management system (Qualtrics), hosted by the University of South Australia which will be the institution that owns the data. There are no plans to transfer the data to other sites.

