**Objectives**

**Custodial health nurses**

1. Establish custodial health nurses' fidelity to BA treatment.
2. Explore custodial health nurses' experiences of delivering BA treatment to people in custody supported by telehealth.
3. Explore the custodial health nurses' experiences receiving co-delivered tele-trial BA training and supervision.

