**Potential Conflict of Interest**

Potential conflict of interest could arise from a preference for positive outcomes. This includes the custodial health nurses being invested in positive outcomes for their patients, and investigators being invested in a positive outcome of the trial. To minimise these potential conflicts of interest, custodial health nurses will be supervised to ensure fidelity to the treatment. The trial team includes members who are not familiar with behavioural activation and have no preconceptions regarding potential outcomes (including benefits) of the treatment. In addition, the establishment of the trial steering group will ensure that the research team is held to account for meeting the trial objectives, monitoring possible breaches, and reporting any safety concerns.

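### A trainer and supervisor of the nurses can identify their interviews about that training and supervision, so these accounts may be less candid

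*Protocol*

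**What the plan says.** **Training and supervision (Protocol, BA training).** Three BA experts, the principal investigator among them, "facilitate the training". The nurses then deliver BA "with supervision being provided via telehealth by" the same three.

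**What the nurses are asked.** The third nurse objective is to explore their "experiences receiving co-delivered tele-trial BA training and supervision"; the second concerns their experience of delivering BA with telehealth support. Process evaluation adds: "The custodial health nurses will also be invited to share their experience of the supervision provided by the BA experts via a telehealth platform". The topic areas there include what failed and what could be improved.

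**Who handles the data (Data collection and management).** On transcripts: "Transcriptions will be de-identified by the research team before data analysis to ensure anonymity". One chief investigator and the principal investigator "will be responsible for de-identifying the data. This will be done by reviewing and removing direct identifiers". Only these two "will have access to the identification code", and the same two are responsible for any re-identification. Data management post-project completion leaves access with these two alone and sets retention at 15 years.

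**Separation that the plan does provide.** The research tele-trial nurse conducts the interviews, contracted transcribers prepare the transcripts, the other analysing chief investigators see only de-identified data, and an independent researcher validates codes and themes.

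**The concern.** A nurse asked what was wrong with the supervision is being asked about a small group of named people. One of them is among the two who turn the identifiable record into a de-identified one and who hold the key that links it back. A nurse who knows or suspects this has a reason to be guarded. Intervention fidelity gives a second reason: the nurses' own adherence to BA is judged through the same supervision structure.

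At stake is the candour of the evidence for nurse objectives 2 and 3, for which interviews are the only stated source. Criticism that is never voiced cannot be recovered later by transcription, coding or validation of themes.

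**Working it through.** There is no formula or stated figure to reproduce. The check sets the roles side by side and then looks at how far de-identification can protect a speaker.

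**1. Overlap of roles**

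| Task | Who | Principal investigator included? |
|---|---|---|
| BA training | three BA experts | yes, one of three |
| Telehealth supervision | the same three | yes, one of three |
| Nurse interviews | research tele-trial nurse | no |
| Transcription | contracted transcribers | no |
| De-identification | one chief investigator and the principal investigator | yes, one of two |
| Identification code | the same two only | yes, one of two |
| Re-identification | the same two | yes, one of two |
| Access after the trial | the same two only | yes, one of two |

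The other code-holder is not listed under BA training as a trainer or supervisor.

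**2. Size of the group**

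- Target number of nurses (Sample size): 8. Prisons (Setting): 4. Average per prison: 8 / 4 = 2. This is an average; the split by prison is not given.
- Nurses interviewed: four to six under Recruitment, at least six under Process evaluation. Four of eight is 4 / 8 = 50%, and six of eight is 6 / 8 = 75%.

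Between half and three quarters of a group of eight would be interviewed, or more if the minimum of six is exceeded. The stated method removes direct identifiers. In a group this small, a prison, an incident or a turn of phrase left in a transcript may be enough for a supervisor to recognise the speaker. Whoever does the de-identifying has seen the identifiable version in any case.

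**3. What each safeguard reaches**

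- *Separate interviewer.* This is the only safeguard that acts at the interview itself. It is real but incomplete, because Recruitment describes the tele-trial nurse's role as supporting the principal investigator.
- *Independent transcription and validation of themes.* Both act after the interview and protect how the words are recorded and coded. They cannot restore what was withheld.
- *Limit to de-identified data.* It covers the analysing chief investigators and does not stand between the principal investigator and the identifiable record.
- *Potential Conflict of Interest.* It recognises that investigators may favour a positive result, but does not mention this overlap. One of its remedies is supervision of the nurses, which is itself what the nurses are asked to assess.

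**4. Which outcomes are exposed**

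- Exposed: nurse objectives 2 and 3, and the nurse interviews in the process evaluation.
- Not exposed: treatment acceptability. The section on the quality-of-life outcome states that it is determined from interviews with people in custody, whom the principal investigator neither trains nor supervises in BA.
- Not exposed: recruitment, randomisation, session attendance, completion of measures, PHQ-9 and SF-36.

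**The case against.** The strongest case against the point is that the plan already separates the roles to a fair degree. The tele-trial nurse contacts the nurses about interviews and conducts them. The nurses are employed by the local health network, and no line management by the principal investigator is stated. Transcripts are de-identified by the research team, so nothing fixes that the principal investigator personally handles any nurse transcript. Nor can we see what the nurses are told, because the consent material is not in the text at hand.

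Most of this stands, and it limits the claim. It does not remove it: the plan permits a supervisor to hold the identifiable record and the key, and no provision excludes this for the nurse interviews.

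Three stronger readings are tempting and are not supported.

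- A reader might infer that nurses report to the person they judge. They speak to a separate interviewer; the principal investigator's possible access comes afterwards.
- A reader might infer that acceptability of BA will be overstated. Treatment acceptability comes from people in custody. The abstract and the process evaluation heading do link nurse interviews to acceptability, but only that nurse component is exposed, and no evidence fixes the size of any distortion.
- A reader might add the principal investigator's first email to nurses to the case. That email concerns joining the trial, not the interviews, and has no bearing on what is said in them.

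**Conclusion.** The point holds in a limited form. One of the three people who train and supervise the nurses is also one of the two who de-identify the data and hold the code. With a target of eight nurses over four prisons, the nurses' accounts of training and supervision can be identified by a person they are judging, and so may be less candid.

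The effect is on nurse objectives 2 and 3 only. Its size cannot be calculated: the planned analysis is thematic, no dissatisfaction rate is to be estimated, and the documents give no basis for assuming how many nurses would hold back. If there is an effect, withheld criticism would make training and supervision look better than nurses found them.

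The conclusion rests on two assumptions: that nurses know or suspect who has access, and that removing direct identifiers does not reliably disguise a speaker in so small a group. Both are reasonable, but neither is shown by the documents. This is a cheap improvement to a qualitative component and does not threaten the feasibility results.

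**What to change.** Amend Data collection and management and Data management post-project completion, for the custodial health nurse interviews only:

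- Assign recordings, identifiable transcripts, de-identification and the nurse code to the chief investigator already named as second code-holder, or to another team member, provided that person is not a BA trainer or supervisor. Potential Conflict of Interest indicates where others may be found: "The trial team includes members who are not familiar with behavioural activation and have no preconceptions regarding potential outcomes".
- Keep the nurse code separate from the code for people in custody.
- Let trainers and supervisors see only de-identified material, stripped of details of prison and role, and only once coding is final. Apply the same limit after the trial.
- Make sure nurses are told this before interview. The information sheet could not be checked, so this may need confirming rather than adding.

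Arrangements for data from people in custody stay as they are; the argument gives no reason to take that code from the principal investigator.

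The cost is protocol wording, possibly information-sheet wording, and some added work for someone already on the team, whose capacity the documents do not show. The drawback is that only one of the two named people could then re-identify nurse interview data. A second holder from outside the training and supervision group would remove that dependence.
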